## Abstract

**Background:**

This article describes the design of a parallel-group, participant- and assessor-blinded randomised controlled trial comparing the effectiveness of shoe-stiffening inserts versus sham shoe insert(s) for reducing pain associated with first metatarsophalangeal joint (MTPJ) osteoarthritis (OA).

**Methods:**

Ninety participants with first MTPJ OA will be randomised to receive full-length shoe-stiffening insert(s) (Carbon Fibre Spring Plate, Paris Orthotics, Vancouver, BC, Canada) plus rehabilitation therapy or sham shoe insert(s) plus rehabilitation therapy. Outcome measures will be obtained at baseline, 4, 12, 24 and 52 weeks; the primary endpoint for assessing effectiveness being 12 weeks. The primary outcome measure will be the foot pain domain of the Foot Health Status Questionnaire (FHSQ). Secondary outcome measures will include the function domain of the FHSQ, severity of first MTPJ pain (using a 100-mm Visual Analogue Scale), global change in symptoms (using a 15-point Likert scale), health status (using the Short-Form-12® Version 2.0 and EuroQol (EQ-5D-5L™) questionnaires), use of rescue medication and co-interventions, self-reported adverse events and physical activity levels (using the Incidental and Planned Activity Questionnaire). Data will be analysed using the intention-to-treat principle. Economic analysis (cost-effectiveness and cost-utility) will also be performed. In addition, the kinematic effects of the interventions will be examined at 1 week using a three-dimensional motion analysis system and multisegment foot model.

**Discussion:**

This study will determine whether shoe-stiffening inserts are a cost-effective intervention for relieving pain associated with first MTPJ OA. The biomechanical analysis will provide useful insights into the mechanism of action of the shoe-stiffening inserts.

**Trial registration:**

Australian New Zealand Clinical Trials Registry, identifier: ACTRN12616000552482. Registered on 28 April 2016.

**Electronic supplementary material:**

The online version of this article (doi:10.1186/s13063-017-1936-1) contains supplementary material, which is available to authorized users.

## Background

First metatarsophalangeal joint (MTPJ) osteoarthritis (OA) (*International Classification of Diseases* (ICD-10) code M20.20) is a common degenerative disorder of the foot estimated to occur in 7.8% in people aged 50 years or older, with a higher prevalence observed in women, older people, and those from lower socioeconomic backgrounds [1]. First MTPJ OA is characterised by localised pain and stiffness [2]. This condition is associated with a significant reduction in both foot-specific and general health-related quality of life [3], with 71% of people with first MTPJ OA reporting it to be disabling [1]. Increasing radiographic severity of first MTPJ OA is associated with an increased prevalence of pain, deformity and decreased joint range of motion, suggesting that it may be a progressive disorder which has an accumulative impact on surrounding structures and the load-bearing function of the foot [4].

There are structural changes (joint-space narrowing and the formation of osteophytes at the dorsal aspect) that characterise first MTPJ OA and lead to a restriction in dorsiflexion motion at the joint. This restriction in motion has been speculated to be a key factor in the development of symptoms of first MTPJ OA by causing dorsal compression of the joint during the propulsive phase of gait when the first MTPJ is required to dorsiflex [5]. In addition, the restricted joint dorsiflexion that occurs in first MTPJ OA is associated with overloading of the hallux and lesser forefoot during propulsion [6, 7], as well as a shortened step length and longer stance phase duration [8]. These changes may lead to the development of secondary musculoskeletal complaints.

The treatment goals for first MTPJ OA are to reduce pain and stiffness, as well as to prevent further degeneration of the joint [9, 10]. However, there are no evidence-based guidelines for the management of this condition. Nonetheless, nonsurgical management is recognised as the first-line therapy for this condition [11], with numerous interventions recommended, including pharmaceutical interventions, rehabilitation therapy, taping, footwear modifications and orthotic devices (such as foot orthoses or insoles) [12].

Despite the broad range of treatment options for this disorder, very few have undergone rigorous scientific evaluation [12]. Consequently, the choice of intervention for this condition is frequently a matter of trial and error, leading to increased costs and prolonged disability. The existing evidence suggests that a 4-week supervised rehabilitation therapy programme involving first MTPJ mobilisation, toe-flexor strengthening, and gait retraining alleviates symptoms of first MTPJ OA (magnitude of pain measured using a 0 to 10 pain scale reduced from 6.8 ± 1.5 to 0.4 ± 0.5) [13]. We have also found that prefabricated arch-contouring foot orthoses with a cut-out beneath the first MTPJ are equally effective as rocker-sole footwear (footwear that has a rounded sole) for reducing foot pain in people with this condition [14]. However, despite the positive symptom-modifying effects of these interventions, approximately 50% of participants either had no change or worsened [14], indicating that there is a need to further study other potential interventions for this condition.

Shoe-stiffening inserts are also commonly recommended as an intervention for first MTPJ OA [12]. Shoe-stiffening inserts are made from a thin, semi-rigid material that is placed inside the shoe with the objective of reducing the rate and magnitude of dorsiflexion at the MTPJ during the propulsive phase of gait [15, 16]. This action is speculated to reduce the symptoms of first MTPJ OA by decreasing the amount of motion and the resultant dorsal compression at the first MTPJ that occurs during propulsion [15, 16]. Indeed, there is evidence to suggest that shoe-stiffening inserts can reduce dorsiflexion of the first MTPJ during gait [17]. Importantly, there is also evidence to suggest that shoe-stiffening inserts may be effective at reducing the symptoms of first MTPJ OA. Our recent case-series feasibility study of 31 participants with first MTPJ OA found clinically worthwhile improvements in foot pain and foot-related disability at 3 months [18]. Further, 78% of participants reported that the shoe-stiffening inserts were effective. Whilst these findings are promising, there is now a need to conduct a rigorous randomised controlled trial and economic analysis to evaluate whether this simple, noninvasive and relatively low-cost intervention is effective. There is also a need to determine the effects of this intervention on foot function in this cohort to understand the potential mechanism(s) of action. Therefore, the primary aim of this project is to determine whether shoe-stiffening inserts are more effective at reducing pain of the first MTPJ in people with first MTPJ OA compared to sham shoe inserts. The secondary aims are to determine (1) whether shoe-stiffening inserts are more effective at reducing first MTPJ dorsiflexion range of motion when walking compared to sham shoe inserts and (2) whether shoe-stiffening inserts are a more cost-effective treatment for first MTPJ OA compared to sham shoe inserts.

## Methods

This study protocol has been reported using the Standard Protocol Items: Recommendations for Interventional Trials (SPIRIT) guidelines [19], and the associated checklist is included as Additional file 1.

### Design

This study is a parallel-group, participant- and assessor- blinded, randomised controlled trial with a 52-week follow-up (Fig. 1). Participants will be randomised to an experimental group (shoe-stiffening insert(s) (Carbon Fibre Spring Plate, Paris Orthotics, Vancouver, BC, Canada) or a control group (sham shoe insert(s)). To ensure that all participants, who will have some level of pain and disability, receive some form of intervention, both groups will also be prescribed the same rehabilitation therapy programme. This design covers any ethical concerns of not treating participants in pain, but will allow the effectiveness of the shoe-stiffening inserts to be evaluated.

**Fig. 1 Fig1:**
[figure not shown]
Trial profile

Due to the nature of the intervention, research staff administering the shoe insert(s) cannot be blinded to group allocation. However, research staff prescribing the rehabilitation therapy (see later), assessing outcomes and entering and analysing data will be blinded. Further, participants will be blinded to their group allocation by being informed that they will receive one of two different shoe insert treatments and a rehabilitation therapy programme for their condition.

Assessments will be performed at the La Trobe University Health Sciences Clinic, Bundoora (VIC, Australia) and the La Trobe University Gait Laboratory, Bundoora (VIC, Australia).

The study has been developed using the principles described by Osteoarthritis Research Society International (OARSI) Clinical Trials Task Force guidelines [20] and recommendations for the conduct of efficacy trials of treatment devices for OA by the Arthritis Research UK Osteoarthritis and Crystal Diseases Clinical Studies Group [21]. Publications associated with the trial will be reported according to the Consolidated Standards of Reporting Trials (CONSORT) 2010 Statement [22, 23]. The study has been registered with the Australian New Zealand Clinical Trials Registry (ACTRN12616000552482).

### Ethics approval

Ethics approval has been granted from the La Trobe University Human Ethics Committee (number HEC15-128). Informed consent will be obtained from all participants. Ethical standards will adhere to the National Health and Medical Research Council (NHMRC) National Statement [24] and the World Medical Association’s Declaration of Helsinki [25].

### Participant recruitment and eligibility criteria

Participants will be recruited by advertisements placed in local newspapers, by posters placed in senior citizens’ centres and retirement villages, mail-out advertisements to health care practitioners in Melbourne, mail-out to people currently accessing podiatry services at the La Trobe University Health Sciences Clinic, and through social networking media (e.g. Facebook, Twitter).

#### Inclusion criteria

To be included in this study, participants must: (1) be aged at least 18 years, (2) report having pain in the first MTPJ on most days for at least 12 weeks, (3) report having pain rated at least 30 mm on a 100-mm Visual Analogue Scale (VAS), (4) have pain upon palpation of the dorsal aspect of the first MTPJ and restricted first MTPJ dorsiflexion (less than 64° of dorsiflexion range of motion) [26], (5) be able to walk household distances (more than 50 m) without the aid of a walker, crutches or cane, (6) be willing to have their foot X-rayed, (7) agree to attempt to not receive additional interventions (such as shoe modifications, physiotherapy, foot orthoses, intra-articular injections, or surgery) for the first MTPJ pain during the course of the study, (8) be able to reach their feet to perform ‘rehabilitation therapy’ of the first MTPJ and (9) be willing to attempt to discontinue consuming any pain relieving medications for first MTPJ OA (except paracetamol (up to 4 g per day) which will be rescue medication) for at least 14 days prior to the baseline assessment and during the study period. Participants who consume paracetamol for first MTPJ pain prior to recruitment will be advised to discontinue its use at least 24 h prior to the baseline assessment and follow-up assessments at 4, 12, 24 and 52 weeks.

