### Outcome measures

Primary and secondary outcome measures will be collected at baseline and at 4, 12, 24 and 52 weeks. These time points have been selected as 4 weeks is considered the earliest time to detect an effect, 12 weeks is considered to be a clinically feasible time point when maximum effect would be expected and is, therefore, the primary endpoint [21, 37], and 24 and 52 weeks will allow us to determine the longer-term effects of the interventions [38]. To minimise participant burden, postal questionnaires will be used for the weeks 4, 24 and 52 assessments. To minimise loss of follow-up data, participants who do not return questionnaires will be reminded up to three times to return their questionnaires.

Biomechanical analyses will be performed at 1 week: this will minimise participant burden during the baseline assessment and enable some level of habituation to the interventions.

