#### Secondary outcome measures

The secondary outcome measures will include:Foot-related disability (using the foot function domain of the FHSQ) [39]Severity of pain at the first MTPJ whilst walking over a flat surface and during rest over the past week (each via a 100-mm VAS)Self-reported magnitude of symptom change (using a 15-point Likert scale where the responses range from ‘a very great deal better’ to ‘a very great deal worse’). This variable will then be dichotomised into the categories of ‘effective’ (‘a very great deal better’, ‘a great deal better’, ‘a good deal better’, ‘moderately better’) and ‘ineffective’ (‘somewhat better’, ‘a little better’, ‘about the same, hardly any better at all’, ‘no change’, ‘about the same, hardly any worse at all’, ‘a little worse’, ‘somewhat worse’, ‘moderately worse’, ‘a good deal worse’, ‘a great deal worse’, ‘a very great deal worse’) [14]Level of physical activity (using the using the Incidental and Planned Activity Questionnaire (IPAQ)) [43]Health status (using the Short-Form-12 Version 2 (SF-12®) questionnaire [44] and EuroQol (EQ-5D-5L™) questionnaire [45])The use of paracetamol rescue medication (number of participants and mean consumption) and co-interventions to relieve pain at the first MTPJ, documented with a monthly diary throughout the 52-week study period [14, 37, 46]

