### Sample size

The sample size has been determined a priori using SPSS Sample Power 3.0 (IBM Corp., Armonk, NY, USA) based on the FHSQ pain domain as the primary outcome measure. Using a power of 90%, minimal important difference of 12.5 points in the foot pain domain of the FHSQ [37, 54], SD of 16.8 (based on the 12-week time point in our recent trial [14]), assuming a 10% dropout rate, and a significance level set at *α* < 0.05, we estimated that a total of 90 participants will be required.

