### Statistical analysis

Statistical analysis will be performed using the most recent version of SPSS (IBM Corp., Armonk, NY, USA) available at the time of analysis. Analysis will adhere to the intention-to-treat principle for all randomised participants. In participants with bilateral symptoms, the more painful foot will be analysed (or the right foot if they cannot define the more painful foot) to maintain independence of data. Multiple imputation will be used to replace any missing data using five iterations, with sex, age, baseline scores and group allocation as predictors. The exception will be for the following variables where no data substitution will be applied: self-reported magnitude of symptom change, use of co-interventions, and adverse events. Standard tests to assess continuous data for normal distribution will be used and transformation carried out if required. The primary outcome measure will be the foot pain domain of the FHSQ measured at 12 weeks. To avoid over-testing and to minimise the risk of type I error associated with serial measurements, statistical analysis of the effectiveness of the interventions will specifically focus on the change in primary outcome measures between baseline and 12 weeks [55, 56], and differences in the primary and secondary outcome measures between the two groups will be compared at 12 weeks. Continuously scored outcome measures (FHSQ foot pain domain, FHSQ foot function domain, severity of pain at the first MTPJ whilst walking over a flat surface and during rest in the previous week, level of physical activity using the IPAQ, and health status using the SF-12® and EQ-5D-5L™) will be analysed using analysis of covariance with the intervention group and baseline scores entered as independent variables. Self-reported magnitude of symptom change will be compared using relative risk, risk difference and number needed to treat (NNT). Use of paracetamol rescue medication and intervention adherence will be compared using independent groups *t* tests. Use of co-interventions and frequency of adverse events will be compared using relative risk and risk difference statistics. For the biomechanical evaluation, first MTPJ range of motion and maximum first MTPJ dorsiflexion will be compared between groups using analysis of covariance with the intervention group and shoe-only condition scores entered as independent variables.

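### The 24 h paracetamol stop before each assessment is worded for pre-recruitment users only, although paracetamol is the rescue drug for everyone

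*Protocol article*

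**What the plan says.** Two adjoining statements in the Inclusion criteria matter.

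- Criterion 9 asks participants to try to stop other pain relievers for first MTPJ OA. Paracetamol, up to 4 g per day, is the exception, "which will be rescue medication) for at least 14 days prior to the baseline assessment and during the study period". Access is not limited to people who used it before.
- The next sentence sets the stop, and names whom it is for: "Participants who consume paracetamol for first MTPJ pain prior to recruitment will be advised to discontinue its use". The stop lasts a minimum of 24 h and is required ahead of every outcome visit, baseline included; the sentence lists the visits as "prior to the baseline assessment and follow-up assessments at 4, 12, 24 and 52 weeks".

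Three other sections bear on how this works in practice.

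- Outcome measures: "postal questionnaires will be used for the weeks 4, 24 and 52 assessments". The 12-week assessment, which is the primary endpoint, is not on that postal list.
- Secondary outcome measures: a monthly diary records rescue use, "The use of paracetamol rescue medication (number of participants and mean consumption" being the planned summaries.
- Statistical analysis: "Use of paracetamol rescue medication and intervention adherence will be compared using independent groups" *t* tests. The primary model for FHSQ foot pain at 12 weeks is an analysis of covariance on group and baseline score, with no term for rescue use.

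**The concern.** A stop tied to each assessment has an evident purpose: pain should not be scored under recent paracetamol. The rule gives its population, duration and visits, but that population is smaller than the group allowed the drug. Someone who first takes paracetamol after enrolment may use it up to and on the day of the 12-week assessment without departing from any instruction in the article.

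Whether someone used paracetamol before recruitment is fixed before allocation. Whether someone starts it afterwards is not, and symptoms plausibly drive it. If the stiffening insert relieves pain, more new users would be expected in the sham arm. Higher FHSQ scores mean less pain, so analgesia there would raise the sham scores and narrow the difference. If the stiff insert causes discomfort instead, the imbalance and the bias would run the other way. The between-arm comparison of paracetamol use could reveal an imbalance, but it would not make the conditions of assessment alike.

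**Working it through.** The plan states no figure on this point. The nearest one, the sample size, reproduces closely. With a difference of 12.5, SD 16.8, power 90% and α 0.05 (taken as two-sided, equal arms), a *t*-based calculation gives 39 per arm. Then 39 / 0.9 = 43.3, so 44 per arm and 88 in all, against 90 stated. The point concerns wording and does not rest on this.

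**Step 1. Who is covered, on the text as it stands**

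| First paracetamol use for first MTPJ pain | Allowed as rescue? | Advised to stop 24 h before week 12? |
|---|---|---|
| Before first contact with the trial | Yes | Yes |
| Between first contact and enrolment (includes the 14-day run-in) | Yes | Yes if recruitment means enrolment, no if it means first contact; the article does not define it |
| After enrolment | Yes | No, on either meaning |

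Only the third row is clearly outside the rule. Outcome measures, Secondary outcome measures and Statistical analysis do not extend the stop.

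**Step 2. Does the analysis deal with it?** The baseline score cannot adjust for drug use that begins later. The diary is monthly, and the article does not say that it records use in the 24 h before an assessment.

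**Step 3. Can a size be derived?** To a first approximation,

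reduction in the group difference = (p_sham − p_stiff) × e

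Here p is the proportion of an arm that is uncovered and took paracetamol in the last 24 h, and e is the mean rise in FHSQ pain score per such user. The article gives neither. Purely for illustration, assume an arm difference of 0 to 20 percentage points and e of 5 to 12.5 points:

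- 0 × any e = 0
- 0.10 × 5 = 0.5 points
- 0.20 × 5 = 1.0 point
- 0.10 × 12.5 = 1.25 points
- 0.20 × 12.5 = 2.5 points

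If the arm difference is negative, the sign reverses.

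The recall period matters as well. The VAS items ask about pain "whilst walking over a flat surface and during rest over the past week". If the FHSQ pain domain averaged evenly over seven days, a 24 h stop would affect one day in seven, and the largest value above would become 2.5 / 7 = 0.36 points. The article does not give the FHSQ recall period. The answer thus runs from nothing to a couple of points in either direction, depending wholly on assumed inputs.

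**The case against.** The strongest case on the other side has four parts.

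1. **Shorthand.** The sentence closes a paragraph on eligibility, so it naturally describes people as they present at screening. It lists all the follow-up assessments, which suggests that a stop at every assessment was meant for every user. A journal article also leaves reminders and cover notes to the full protocol. This is fair as to intent, and the reminder line alone would not be a finding. But the article does state the rule and its population, and that population is too narrow. If all users were meant, the rewording only records it.
2. **No contradiction.** A reader might infer that the two statements conflict. They do not: rescue use and a pause before assessments are compatible. The fault is only in who is told to pause.
3. **The switcher.** A reader might take someone who gives up an anti-inflammatory under criterion 9 and turns to paracetamol as a clear example of an uncovered user. The article does not settle that. The switch may fall in the 14 days before baseline, and such a person is covered if recruitment means enrolment.
4. **Power.** A reader might infer a material loss of power. Taking 2.5 points off the planned 12.5 would lower power from about 91% to 75% with 81 completers (90 × 0.9). That needs two assumed extremes together: a 20-point arm difference in uncovered users, and an effect per user equal to the trial's whole "minimal important difference of 12.5 points in the foot pain domain of the FHSQ". It also ignores the gain from baseline adjustment. The documents support neither input, so the figure should not be used.

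It also stands that the stop is only advice, so extending it would not guarantee equal conditions, and that the diary would show a marked imbalance in use.

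**Conclusion.** The point holds as a reading of the text. Rescue paracetamol is open to all throughout the study, while the advice to stop before assessments reaches only pre-recruitment users. People who first take it after enrolment are not covered at the 12-week primary assessment, and how many there are can depend on treatment arm.

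Neither the size nor the direction of any resulting bias can be derived from the article. That would need the rate of new use by arm, the effect of paracetamol on the FHSQ pain score and the score's recall period, and the article gives none of them. The effect may be negligible. This is a cheap clarification of the lowest severity. It does not show that the primary result would be biased or the trial underpowered.

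**What to change.** Reword the sentence along these lines: *Participants who take paracetamol for first MTPJ pain at any time, whether started before or after recruitment, will be advised to stop it at least 24 h before the baseline assessment and before each follow-up assessment.* Give the same reminder to all participants with the week-12 appointment and with the postal questionnaires at weeks 4, 24 and 52.

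Eligibility, permitted drugs, diary content and the intention-to-treat analysis stay as they are. The cost is one sentence and one reminder line, with no new data item or analysis. The downside is that a few more participants would go up to 24 h without rescue medication before an assessment, a burden the protocol already accepts for earlier users.
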